**Fig 2 pone.0263002.g002:**
[figure not shown]
Study flowchart.

## ● Measured outcomes

The primary outcome is the rated per procedural anxiety, measured by the Spielberger Anxiety State Inventory in French [30]. The Spielberger Anxiety State Inventory is a self-questionnaire of 20 items, each item scores from 1 to 4. The test result is the sum of the 20 items; therefore, the results range from 20 to 80 (Table 1). A high score is related to a high level of anxiety at the moment of the test.

The secondary outcome is the rated per procedural pain measured by the visual analog pain scale. The visual analog pain scale rates pain from 0 to 10, 0 being no pain, and 10 being the worst pain imaginable (Table 2).

Both outcomes will be measured on day 1, before and after the intervention, and 3 months after the intervention.

The other outcomes of interest will be measured on day 1. Those outcomes are age and sex, side effects of virtual reality, the amount of drugs administered for pain and anxiety, the number of participants that did not tolerate the mask before randomization, and the number of participants where the mask has been taken off (patient decision/medical team decision). We will measure the prevalence of cybersickness, our safety outcome on day 1.

Patient-relevant outcomes, including amputation, mesenteric or renal ischemia, and death, will be reported 90 days after EVI.

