### ● Sample size, inclusion, and exclusion criteria

A power analysis was conducted to determine a sample size that can detect a statistically significant anxiety decrease of at least 5 percent, such as encountered in a previous investigation using autohypnosis in the setting of systemic chemotherapy [29]. The Sample size calculation is based on the primary outcome "per procedural anxiety". The expected mean (sd) of per procedural anxiety in the control group is 45 (3) and 5% lower in the intervention group 42.75 (2). The minimum sample size needed to show that the mean difference is significant with a power of 90% and an alpha of 5% (two-sided) is 32 patients per group. To avoid loss of power due to possible dropout (20%), randomizing 40 patients in each group would be appropriate. Furthermore, because the primary outcome measure is patient-reported and subject to measurement error, we intend to add a safety margin and include 50 participants in each group since no additional risk nor financial burden is associated with study participation.

Inclusion criteria: participants will be patients subjected to interventional radiology for a peripheral vascular intervention under local anesthesia; participants will be over 18 years old and have signed an informed consent form. In this study, peripheral EVI refers to lower limb arterial angioplasty and stenting, renal and mesenteric angioplasty and stenting, venous interventions (vena cava filter placement, venous malformation embolization, peripherally inserted central catheter). Patients referred to cardiothoracic or neuroradiology intervention are not eligible.

Exclusion criteria: no or limited study language comprehension, deafness or visually impaired patient, the anticipated need for a sedative medication, a history of motion sickness or a psychiatric disease such as paranoia, schizophrenia, deep water phobia, and dementia. We will also exclude patients who do not tolerate the virtual reality mask during a preoperative visit.

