**Fig 1 pone.0263002.g001:**
[figure not shown]
Schedule of enrolment, interventions, and assessments.

**Table 1 pone.0263002.t001:** Anxiety scale used before and after the endovascular intervention.

		Not at all	A little	Somewhat	Very much so
**1.**	I feel calm	**1**	**2**	**3**	**4**
**2.**	I feel secure	**1**	**2**	**3**	**4**
**3.**	I feel tense	**1**	**2**	**3**	**4**
**4.**	I feel strained	**1**	**2**	**3**	**4**
**5**	I feel at ease	**1**	**2**	**3**	**4**
**6.**	I feel upset	**1**	**2**	**3**	**4**
**7.**	I am worrying about possible misfortunes	**1**	**2**	**3**	**4**
**8.**	I feel satisfied	**1**	**2**	**3**	**4**
**9.**	I feel frightened	**1**	**2**	**3**	**4**
**10.**	I feel comfortable	**1**	**2**	**3**	**4**
**11.**	I feel self-confident	**1**	**2**	**3**	**4**
**12.**	I feel nervous	**1**	**2**	**3**	**4**
**13.**	I feel jittery	**1**	**2**	**3**	**4**
**14.**	I feel indecisive	**1**	**2**	**3**	**4**
**15.**	I am relaxed	**1**	**2**	**3**	**4**
**16.**	I feel content	**1**	**2**	**3**	**4**
**17.**	I am worried	**1**	**2**	**3**	**4**
**18.**	I feel confident	**1**	**2**	**3**	**4**
**19.**	I feel steady	**1**	**2**	**3**	**4**
**20.**	I feel pleasant	**1**	**2**	**3**	**4**

This questionnaire will be presented to participants in the French language, according to Gauthier et al. [30].

**Table 2 pone.0263002.t002:** Pain assessment scale used before and after the endovascular intervention.

Absence of pain	**1**	**2**	**3**	**4**	**5**	**6**	**7**	**8**	**9**	**10**	Worst pain imaginable

Participants will be asked to indicate the pain they currently feel on the pain scale (0 = absence of pain; 10 = worst pain imaginable).

The percutaneous EVI is performed as usual except for the autohypnosis software that will run during the intervention in the virtual reality group.

The medical team will provide pain and anxiolytic medication if needed during the intervention at the operator’s discretion and depending on the patient’s condition.

Immediately after the intervention, participants will fill a second self-questionnaire (postoperative questionnaire) to report anxiety and pain felt during the intervention (Tables 1 and 2).

A clinical visit at 3 months, as part of the standard clinical protocol, is planned for late assessment. Participants will fill a third self-questionnaire on anxiety (Table 1), the visual analog scale for pain (Table 2), and remembered per-procedural impressions (Table 3).

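### The primary anxiety score is defined as a plain sum of Table 1, where 11 of 20 items describe calm and no reversal is stated, so the rule contradicts its own direction

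*Protocol article*

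**What the plan says.** Measured outcomes names the endpoint and the instrument: "The primary outcome is the rated per procedural anxiety, measured by the Spielberger Anxiety State Inventory in French [30". It then describes the items, "The Spielberger Anxiety State Inventory is a self-questionnaire of 20 items, each item scores from 1 to 4", and gives the rule for the total, "The test result is the sum of the 20 items; therefore, the results range from 20 to 80 (Table 1". The direction follows at once: "A high score is related to a high level of anxiety at the moment of the test".

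Table 1, to which the rule refers, prints the 20 items with one set of response codes, 1 = not at all to 4 = very much so, the same for every row. Its footnote adds: "This questionnaire will be presented to participants in the French language".

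The sample size section relies on this score: "The expected mean (sd) of per procedural anxiety in the control group is 45 (3) and 5% lower in the intervention group 42.75 (2". The article mentions no reverse scoring anywhere.

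**The concern.** The printed items point in two directions. Eleven describe calm or well-being: 1 (calm), 2 (secure), 5 (at ease), 8 (satisfied), 10 (comfortable), 11 (self-confident), 15 (relaxed), 16 (content), 18 (confident), 19 (steady) and 20 (pleasant). Nine describe anxiety: 3, 4, 6, 7, 9, 12, 13, 14 and 17. An anxious patient answers low on the first group and high on the second, so a plain sum sets one group against the other. The rule for the total and the stated direction of the score cannot both hold for the printed table.

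This is the primary outcome, the only variable behind the sample size, and it is scored the same way before the procedure, after it and at 3 months. Anyone who programmed the derivation from the published text would build a variable that barely responds to the effect the trial is looking for. A range check would not reveal the error, because the limits of 20 and 80 are the same with or without reversal.

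**Working it through.** **Inputs.** Item wording and codes: Table 1. Rule and direction: Measured outcomes. Planning means of 45 (control) and 42.75 (intervention): sample size section. One simplifying assumption: a consistent respondent at anxiety level *a* (1 to 4) answers *a* on each anxiety-worded item and 5 − *a* on each calm-worded item.

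**Stated range.** 20 × 1 = 20 and 20 × 4 = 80. The range reproduces. Under the plain sum, however, 20 requires answering 1 to everything (neither calm nor tense) and 80 requires answering 4 to everything (fully calm and fully tense). The ends are reached only by self-contradictory answers.

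**Plain sum as written, 11 calm and 9 anxious items.**

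- Sum = 11(5 − *a*) + 9*a* = 55 − 2*a*.
- Calmest (*a* = 1): 11 × 4 + 9 × 1 = 53.
- Most anxious (*a* = 4): 11 × 1 + 9 × 4 = 47.
- The whole span is 53 − 47 = 6 points, against the stated direction.

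**Sum with calm items recoded as 5 minus the response.**

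- Each recoded calm item is 5 − (5 − *a*) = *a*, so the sum is 20*a*.
- Calmest: 20. Most anxious: 80. Range and direction now agree.

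**Planned effect under each rule.**

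| | Anxiety level *a* | Recoded sum, 20*a* | Plain sum, 55 − 2*a* |
|---|---|---|---|
| Control | 45/20 = 2.25 | 45.00 | 50.500 |
| Intervention | 42.75/20 = 2.1375 | 42.75 | 50.725 |
| Difference | −0.1125 | −2.25 | +0.225 |

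The plain sum keeps one tenth of the planned difference, with the opposite sign.

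**Sensitivity to item 18.** As printed, it reads "I feel confident", which nearly repeats item 11. If the French form has an anxiety-worded item there, the split is 10 and 10, and the plain sum is 10(5 − *a*) + 10*a* = 50 for every *a*. Both extremes score 50 and the planned difference becomes 0.

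**Which rule the planning means fit.** Consistent respondents under the plain sum lie between 47 and 53. Both 45 and 42.75 fall below that interval, while both are ordinary values on the recoded scale.

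**Whether a stored total can be repaired.** Let C be the raw sum of the 11 calm items and A that of the 9 anxious items. The plain total is C + A and the recoded total is 55 − C + A. They differ by 2C − 55, so a stored plain total cannot be converted without the item responses.

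**The case against.** The best defence is that the article names an existing questionnaire and does not construct a new score. Recoded items still score 1 to 4 and still total 20 to 80, so the scoring sentences can be read as describing item scores after recoding. The stated direction and the planning means both fit that reading. A condensed article may also leave scoring detail to the questionnaire's instructions, the full protocol or the analysis plan, none of which is shown.

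Much of this stands. Silence on recoding would be no finding by itself, and reversal was probably intended. What the defence does not remove is that the article gives a rule for the total and ties it to a table whose printed codes all run one way. Applied to that table, the rule contradicts the direction stated in the next sentence.

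Two stronger readings are tempting and go too far. A reader might infer that the score runs backwards, so that a real benefit would show up as harm. That sign depends wholly on item 18 as printed in English. Participants answer a French form that is not shown, and with a 10/10 split the score is flat, not reversed. A reader might also infer that the trial's data are mis-scored. Nothing in the document shows how the database computes the total.

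Nor can the document support a figure for lost power. That would need assumptions about how the items correlate and how far responses spread, which the article does not give.

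**Conclusion.** The point holds as an internal contradiction in the definition of the primary endpoint: the rule, followed literally on Table 1, yields a score with almost no information on anxiety. The calm-to-anxious span is 6 points (53 to 47) instead of 60 (20 to 80), or zero if item 18 is anxiety-worded in French. The planned 2.25-point reduction becomes a rise of about 0.2, or no change.

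The item count and the extreme scores come straight from the printed table. The translation of the planned effect assumes consistent respondents; real answers will scatter around these values, but the cancellation between the two blocks remains. The case for intended reversal is strong but indirect, and whether actual data are affected is unknown. Because this is the primary outcome and the correction costs so little, it should be made before the score is derived for analysis.

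**What to change.** 1. Add to the outcome definition: calm-worded items (1, 2, 5, 8, 10, 11, 15, 16, 19 and 20, and 18 if it is calm-worded on the French form) are recoded as 5 minus the response; the score is the sum of the 20 items after recoding, from 20 to 80, with higher values meaning more anxiety.
2. Check item 18 against the French form, score it by its actual wording, and correct Table 1 if the printed English is wrong.
3. Confirm that the REDCap or analysis derivation applies the recoding at all three time points. Two test records suffice: a fully calm one must score 20 and a fully anxious one 80.

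The cost is one sentence, one line of derivation code and one check of the form. Data already collected can be rescored if item responses were stored. Data management does not say whether they were, so this should be confirmed as well.

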## Introduction

Endovascular interventions (EVI) are minimally invasive therapies gaining interest in many indications. EVI are increasingly replacing surgery and vastly reduce the need for general anesthesia. Indications for percutaneous interventions are many and varied; typical examples include treatments for venous disorders [1], aneurysms [2], and peripheral and visceral arterial diseases [3]. Interventions whose sole purpose is to gain vascular access, such as for peripherally inserted central catheters, are performed exclusively under local anesthesia [4]. Furthermore, outpatient procedures have been developed and expanded during the last decade [5]. Despite efforts regarding patient information, preparation, and management for EVI, patients often experience periprocedural apprehension, generating anxiety. During peripheral EVI–procedures primarily performed under local anesthesia–pain feelings at various levels are observed. Such states are not specific to EVI and have frequently been reported in patients admitted for cardiovascular surgery, ranging from 20% to 60% [6, 7]. Nonetheless, they might be exacerbated by the environment required for EVI, which includes complex facilities (X-ray and hybrid interventional suites), advanced devices and technologies. Associated uncontrolled overcommunication on social media and free websites by non-healthcare professionals, whose quality is variable, might induce ambiguity and inconsistency, leading to anxiety [8]. Furthermore, preoperative anxiety significantly influences postoperative pain and patient outcomes [9, 10], particularly because anxiety and pain interact synergistically.

Periprocedural anxiety and pain are most commonly managed with rapid-acting opioid analgesics and/or hypnotic sedative drugs [11–14]. With minimal (Level 1 of the American Society of Anesthesiology [15]) and moderate sedation/analgesia (Level 2), spontaneous ventilation and cardiovascular function are usually maintained. In contrast, more profound sedation (Level 3) might require intervention for adequate ventilation. Despite appropriate delivery of drugs and careful monitoring, complications may occur. Complications include respiratory depression, hypotension, unconsciousness, paradoxical agitation, and nausea or vomiting. Preprocedural anxiety might be treated with anxiolytics. However, some drugs (e.g., Lorazepam) failed to decrease preoperative anxiety significantly [11].

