### ● Characteristics of participants, randomization, and blinding

The sequentially numbered, opaque, sealed envelope (SNOSE) method was used for randomization with a 1:1 allocation before the intervention. A person not involved with patient recruiting will print the allocation sequence and prepare the envelopes ([name]).

One group of participants will wear the virtual reality mask with the autohypnosis program running during the EVI. The other group will benefit from the intervention in standard conditions without the virtual reality mask.

The study will run in an open-label fashion because information cannot be withheld from trial participants and operators. Participants included in the virtual reality arm will wear the head-mounted device, and awareness regarding self-hypnosis is inevitable.

Study timetable: the first patient was included in August, 2020. The recruitment is expected to be completed by the end of May, 2022.

All vascular punctures are performed under local anesthesia and using ultrasound guidance. The puncture site depends on the clinical indication and is at the operator’s discretion. The typical vascular access is the common femoral artery for peripheral and visceral arterial interventions. The most common venous accesses are the common femoral vein and brachial veins.

Arterial vascular accesses usually benefit from vascular closer devices, at the operator’s discretion, while venous accesses are controlled by manual compression.

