### ● Safety considerations

To date, in the literature, the only recognized side effect of virtual reality is cybersickness [16], a condition similar to motion sickness but caused by immersion in virtual reality rather than by actual movement.

The prevalence of cybersickness is not known because of the diverse software and hardware that deliver virtual reality.

The manufacturer of the Oncomfort system also warns the users of the potential risks of:

claustrophobiaproblems with orientationsweating of the facesleepiness

The prevalence of the above risks is not known.

The present study intends to compare vascular radiologic interventions with or without a virtual reality mask with a specific program to release stress and tension from patients undergoing certain procedures.

We will collect device deficiencies and adverse events, including all serious adverse events. Adverse events will be thoroughly investigated and documented in the medical record and the case report form (CRF) during the entire study period.

There is no follow-up period needed for this study since virtual reality has no known long-term adverse effect.

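### Cybersickness, the named safety outcome, is defined by its cause, so the planned comparison between arms has a control count of zero by definition and a mask-arm count that rests on unblinded attribution

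*Protocol article*

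**What the plan says.** Measured outcomes names the safety outcome: "We will measure the prevalence of cybersickness, our safety outcome on day 1". The same section lists other day-1 outcomes, one of them also named by cause: "Those outcomes are age and sex, side effects of virtual reality, the amount of drugs administered for pain and anxiety".

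Safety considerations describes cybersickness as "a condition similar to motion sickness but caused by immersion in virtual reality rather than by actual movement". The article gives no symptom list, scale or threshold for it. That section adds the manufacturer's warnings (claustrophobia, orientation problems, facial sweating, sleepiness), says that the frequency of cybersickness and of these risks is unknown, and provides for general collection of adverse events.

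Type of data and statistical analyses lists the occurrence of cybersickness among the qualitative data to be compared between the two groups.

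Two further statements bear on how the outcome is ascertained. On blinding: "The study will run in an open-label fashion because information cannot be withheld from trial participants and operators". On drugs, with no restriction by arm: "The medical team will provide pain and anxiolytic medication if needed during the intervention at the operator’s discretion". The Introduction says of sedative and analgesic drugs: "Complications include respiratory depression, hypotension, unconsciousness, paradoxical agitation, and nausea or vomiting".

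**The concern.** A randomised control group is useful for safety because it shows how often a symptom occurs without the device. That requires an event that can occur in both arms. Cybersickness as defined here cannot occur in a patient without a mask, and neither can a side effect of virtual reality. A nauseated control patient does not count, whatever the severity. A nauseated mask patient counts if the person recording the event, who knows the arm, blames the device.

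The error can go either way. A drug or procedural effect may be recorded as cybersickness, or a true device effect may be put down to a drug. Since the article itself says that the frequency of these effects is unknown, readers are likely to use this trial's figure as evidence, and a planned comparison between arms would make it look controlled.

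**Working it through.** The article gives no figure for this outcome, so there is none to reproduce. The check is first a reading of the sections together, then an illustration.

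**Reading**

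1. Outcome: prevalence of cybersickness on day 1 (Measured outcomes).
2. Definition: a state caused by immersion in virtual reality (Safety considerations).
3. Control arm: standard conditions without the mask (Characteristics of participants, randomization, and blinding).
4. From 2 and 3, the control count is 0 of 50 by definition, not by observation.
5. Analysis: occurrence compared between groups (Type of data and statistical analyses). From 4, the result depends only on how many mask-arm symptoms are attributed to the device.
6. Attribution is unblinded, and drugs may be given in either arm. Nausea or vomiting is named as a drug complication. It is also a plausible feature of a motion-sickness-like state, although the article does not say so.

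**Illustration**

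Inputs: 50 per arm (Sample size, inclusion, and exclusion criteria). Assumptions not in the document: background symptom rate p of 5%, 10% or 20%, equal in both arms; no device effect; every mask-arm symptom attributed to the device. Fisher's exact test serves as a yardstick. It is not the test that the article names, and the choice of test is a separate matter.

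- Expected mask-arm count = 50 × p: 2.5, 5 and 10.
- At 5 of 50, the exact (Clopper-Pearson) 95% CI is 3.3% to 21.8%.
- Two-sided Fisher p-value for k vs 0 = 2 × C(50,k)/C(100,k). For 5 vs 0: 2 × 2,118,760/75,287,520 = 0.056. For 6 vs 0: 2 × 15,890,700/1,192,052,400 = 0.027. Six attributed cases are therefore enough.
- Chance of at least 6 cases, X ~ Binomial(50, p), set against the chance of a significant result when the same symptoms are counted in both arms:

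| Assumed p | Cause-based, full attribution | Same symptoms, both arms |
|---|---|---|
| 5% | 3.8% | 0.7% |
| 10% | 38% | 1.8% |
| 20% | 95% | 2.8% |

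With partial attribution, a fraction a of symptoms is counted and p is replaced by a × p. If half are attributed, 10% acts as 0.5 × 10% = 5% (3.8%), and 20% acts as 10% (38%). In the other direction, if six patients have a true device effect and three are put down to a drug, 6 vs 0 becomes 3 vs 0 (Fisher p = 0.24).

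**The case against.** The strongest reply has four parts.

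- **Adverse events are collected generally.** Safety considerations does not restrict this by arm or cause, so nausea in a control patient can be recorded. This stands. It means that attribution governs the named safety outcome and the side effects of virtual reality, not all safety data. A reader might infer that unblinded attribution decides the whole safety result, or that the control arm is ignored for safety. The text supports neither. However, the article does not say that these events are elicited with the same questions in both arms or compared by arm.
- **The exclusions narrow the overlap.** Patients with an anticipated need for sedatives or a history of motion sickness, and those who do not tolerate the mask beforehand, are excluded. Drugs are given only if needed, and amounts are recorded. This reduces the problem but does not remove it, because drugs remain allowed in both arms.
- **The two symptom lists do not match.** A reader might infer that the article names the same symptoms for drug and device. It does not: no item is on both lists. Nausea reaches cybersickness only through the motion-sickness analogy, and sleepiness is named only for the device. The supported statement is that symptoms may overlap.
- **Detail may sit in the full protocol or case report form.** A symptom list may well be there, and its absence from the article is not the point. The causal definition and the comparison between arms are both in this text, and a symptom list would not help while the causal condition remains.

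Reporting device-specific prevalence descriptively in the mask arm is legitimate. The difficulty is comparing it with an arm where it cannot occur.

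**Conclusion.** The point holds as an internal conflict. The definition in Safety considerations makes the comparison in Type of data and statistical analyses uninformative: one side is fixed at zero and the other depends on unblinded judgement. This conclusion needs no assumed rate.

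The size cannot be derived from the document. The 5 of 50 figure, and the 3.8% to 95% range, rest on assumed background rates of 5% to 20% and on every mask-arm symptom being attributed to the device. They are a worst-case illustration in one direction. A reader might take them as a forecast of false device harm, but nothing in the article supports that, and misattribution can also hide a true effect.

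A reader might also infer that the trial fails to show fewer drug side effects. That is not among its stated aims, which are anxiety and pain, with drug amount recorded as a further outcome. The primary and secondary outcomes are unaffected. The change is worth making because this is the only outcome labelled as the safety outcome and the remedy is small.

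**What to change.** 1. Define the compared day-1 safety outcome by symptom, regardless of cause. Add the same short yes/no list (for example nausea, vomiting, dizziness or orientation problems, sweating, sleepiness, feeling of confinement) to the pre- and post-procedure questionnaires that both arms already complete. Asking beforehand avoids relying on recall for symptoms already present.
2. Report the difference in proportions between arms with a 95% CI.
3. Report attributed cybersickness and other attributed side effects of virtual reality descriptively in the mask arm only, and remove cybersickness from the test between groups.

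Cost: about six items on existing forms and slight patient burden, with no extra visit. Recruitment began in August 2020, so this needs an amendment, and symptom data would come only from participants enrolled after it. The report should state that number. If the case report form already asks both arms the same symptoms, only the definition and analysis text need to change. Participants will still know their arm, so some reporting bias remains; the change removes the judgement of cause, not the open-label design.
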